#### Parent/carer level (collected from one in ten parents/carers)

General worry: State-Trait Anxiety Inventory 6-items short form.^22^DDH-related worry: Infant Hip Worries Inventory.^23^Satisfaction with trial: dimensions of care items from EUROPEP^24^ (table 1).

**Table 1 T1:** Assessments at different time points

	Baseline	At 6 week hip check	Within 2 weeks of intervention	3 month follow-up	15 month follow-up	2 year follow-up
Clinician-level						
Theoretical Domains Framework questionnaire	X		X	X	X	X
GP characteristics questionnaire	X					
Fidelity questionnaire			X	X	X	X
Non-participant observations		X				
Semi-structured interviews			X		X	
Parent/carer-level						
State Trait Anxiety Inventory six item short form			X			
Infant Hip Worries Inventory			X			
EUROPEP			X			
Non-participant observations		X				
Semi-structured interviews			X			
Out-of-pocket-costs questionnaire			X			
EuroQol 5 Dimension Scale (EQ-5D)			X			X
Child Health Utility 9D (CHU 9D)						X
Willingness-to-pay questionnaire					X	

GP, general practitioner.

### Statistical analysis

#### Primary endpoint

We will compare the randomised practices using Poisson mixed models, accounting for extra Poissonian variability by including random intercept terms for practices. The response variable will be the number of clinically insignificant referrals from each practice with an offset in the linear model of the log(e) total number of children checked in each practice, to account for differences in practice size and constitution. The random effect at the practice level will account for overdispersion.

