#### Randomisation

Practices will submit an eligibility form to the clinical trials unit, which will register and randomly allocate (concealed) practices within 48 hours. An independent statistician will coordinate randomisation with an allocation ratio of 1:1 and stratified by practice size (based on observed sizes obtained from expressions of interest—we expect two or three strata).

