### Sample size calculation

We based its calculation on Poisson regression and audit data from the Nottingham area (partially presented in Price *et al*^7^) and University College Hospital (audit of 3 years’ practice, unpublished data): a conservative estimate of the number of infants referred as a consequence of the 6-week check within the recruitment period of 1 year is, on average, 3 per practice. Based on the same data, we estimate that about one in three (or, on average, one per practice) of such referrals is correctly made (‘appropriate’ referrals, defined above as ‘clinically significant’, are a subset of these ‘correct’ referrals). Thus, on average, we expect 2 ‘incorrect’ referrals per practice. These are the ones we seek to reduce, and the intervention should serve to cut them by 50%. Thus we aim to detect a reduction, on average, from 3 to 2 referrals per practice in the intervention arm. To account for correlation within practices, which can also be thought of as overdispersion relative to the underlying Poisson variation, we assumed a between-practice component of variance of 20% of the average Poisson ‘counting’ variance per practice. For 90% statistical power and testing two sided at p=0.05, we need 76 practices per group (15% of this total comprises a safety margin to allow for potential challenges). Average referral rates from the Nottingham (2.8%) and University College Hospital data (2.7%) are very consistent, and suggest a target of about 110 children per practice per year to undergo the 6-week check.

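### Randomisation is stratified by practice size, but the primary Poisson model as described names no stratum term and relies on an exposure offset to handle size: minor, a possible small loss of precision

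*Protocol article*

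**What the plan says.** Under Randomisation, the protocol article specifies "randomisation with an allocation ratio of 1:1 and stratified by practice size". Practice size is the only stratification factor. The levels are to be set from sizes reported in expressions of interest, and the article adds "we expect two or three strata".

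Under Statistical analysis, Primary endpoint, the arms are compared with a Poisson mixed model, "accounting for extra Poissonian variability by including random intercept terms for practices". The response is the count of clinically insignificant referrals per practice. The model has "an offset in the linear model of the log(e) total number of children checked in each practice", and the stated reason for the offset is "to account for differences in practice size and constitution". The section does not mention the randomisation stratum.

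Under Sample size calculation, the article states "For 90% statistical power and testing two sided at p=0.05, we need 76 practices per group" and "we aim to detect a reduction, on average, from 3 to 2 referrals per practice in the intervention arm". It assumes a between-practice variance equal to 20% of the Poisson variance.

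**The concern.** An analysis should normally adjust for the factors by which the trial randomises. Here the text gives the offset the job of dealing with practice size, and an offset can do only part of that job. It fixes the coefficient of log(children checked) at 1, so the model assumes the same referral rate per infant in small and large practices. It removes the effect of having more infants to refer. It does not remove a difference in how readily infants are referred, and it does not adjust for the make-up of a practice.

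If the rate per infant does vary with size, that variation goes into the practice random intercept. Stratified allocation has already balanced it between the arms, but the model-based standard error still counts it as noise. What is at stake is some precision. There is also a practical risk: someone writing the analysis code from this section could take size as fully dealt with and leave the stratum out.

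**Working it through.** **Step 1: the plan's own figure.** The inputs, all from Sample size calculation, are means of 3 and 2 referrals per practice, variance factor 1.2, two-sided 0.05, 90% power, and a 15% margin within the total.

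- n per arm = (1.960 + 1.282)² × 1.2 × (3 + 2) / (3 − 2)² = 63.04, rounded up to 64.
- 64 / 0.85 = 75.3, rounded up to 76.

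The stated 76 per group is reproduced. The formula has no stratum term, so the present point does not change it.

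**Step 2: approximate gain from adjusting.** The primary endpoint counts insignificant referrals, for which the article expects 2 per practice and hopes to halve this to 1. The between-practice variance on the log scale is taken as 0.2 / 3 = 0.067, that is, 20% of the Poisson variance at a mean of 3. The variance contribution per practice is 1/mean + 0.067, summed over the two arms:

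- Unadjusted: (1/2 + 0.067) + (1/1 + 0.067) = 1.633.
- Strata explain none of the 0.067: no change, gain 0%.
- Strata explain half (0.033 per arm): 1.567; √(1.567 / 1.633) = 0.979, gain about 2%.
- Strata explain all of it: 1.5; √(1.5 / 1.633) = 0.958, gain about 4%.

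The last figure is a ceiling for that reading of the overdispersion. If the 20% is applied at a mean of 2 instead, the variance is 0.2 / 2 = 0.1. The unadjusted sum is then 1.7 and the ceiling becomes √(1.5 / 1.7) = 0.939, about 6%. The order of magnitude is the same.

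**Step 3: simulation of the described model.** A Poisson-lognormal mixed model with the log(children) offset was fitted without and with stratum indicators, using 76 practices per arm and 700 replicates per scenario. The following are assumptions that the article does not give: three strata averaging 60, 110 and 160 children, sizes within ±20% of those, allocation balanced within strata, log-scale between-practice variance 0.1, about 2 insignificant referrals per control practice, and an illustrative rate ratio of 0.7 for power.

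| Rate per infant, largest vs smallest stratum | Mean SE under the null, without / with stratum | Type I error, without / with | Power at rate ratio 0.7, without / with |
|---|---|---|---|
| Equal | 0.127 / 0.127 | 5.3% / 5.4% | 73.6% / 73.4% |
| 1.5-fold | 0.126 / 0.124 | 5.3% / 5.7% | 73.3% / 74.0% |
| 2-fold | 0.127 / 0.121 | 3.7% / 4.9% | 73.4% / 76.4% |

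Monte Carlo error is about 0.8 points for type I error and 1.7 points for power. At the two-fold gradient, 0.121 / 0.127 = 0.953, a gain of about 5%. Mean estimates were within 0.005 of zero under the null in both models. At a rate ratio of 0.7 they ranged from −0.351 to −0.362, against ln 0.7 = −0.357, so there is no sign of bias.

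**The case against.** The best defence is that the section is not a closed list of model terms. Even the treatment arm is only implied, the article condenses a fuller protocol, and the strata had not been fixed when it was written. A reader might infer that the model contains nothing beyond arm, offset and random intercept, and hence that the analysis departs from the design. The text does not support that: it excludes no covariate, and it does address size through the offset. This part of the defence stands. It does not meet the narrower point, which rests on what the section says: it credits the offset with accounting for size and constitution, and an offset cannot do that.

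Three further inferences also fail:

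- The offset is not wrong for using infants checked during the trial instead of the size used to stratify. The in-trial count is the correct exposure for a referral rate.
- A stratum term would not correct imbalance within strata. It adjusts for differences between strata, which the stratified allocation already keeps small.
- A larger gain can be computed by adding a two-fold effect between two equal strata, variance (ln 2 / 2)² = 0.12 per arm, to the 0.067: √(1.633 / 1.873) = 0.934, about 7%, or about 13% in variance. That stratum variance is nearly twice the whole between-practice variance taken from the plan, so the plan's own overdispersion does not support the figure. The two-fold scenario in the simulation also adds its gradient to the assumed overdispersion and should be read as illustrative.

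**Conclusion.** The point holds as a minor one. The described model names no stratum term, and the offset it relies on for practice size adjusts for exposure only. The consequence ranges from nil to a slightly conservative analysis. Adjusting shortens the standard error by 0% with equal rates per infant, about 2% if strata explain half of a between-practice variance of 0.067, at most about 4% if they explain all of it, and about 5% at the assumed two-fold gradient, where power rises by about 3 points. Which of these applies is unknown, because the article gives no referral rates by practice size.

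A reader might suspect a threat to validity. The check shows none: leaving the stratum out produced neither bias nor type I inflation.

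**What to change.** State that the randomisation size stratum (two or three levels) enters the primary Poisson mixed model as a fixed effect, alongside arm, the log(children checked) offset and the practice random intercept. Reword the purpose of the offset so that it covers exposure only. If the full protocol or analysis plan already lists the stratum, only the rewording is needed. The stratum is known for every practice at randomisation, so the cost is one model term and one sentence, with no new data and no change to the sample size. It should be settled before outcome data are seen.

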#### Principal secondary endpoint

#### Late diagnoses

As we anticipate small numbers of events in each randomised comparison we may not be in a position to account for practices using random intercept terms. Where this is the case we will report the total numbers over a minimum 2-year observation and compare the overall group scores using Fisher’s exact test.

#### Quantitative outcome measures

We will summarise scores by instrument, accounting for practices and report difference in group means for each treatment arm. We expect mean scores to be lower in the intervention arm for State-Trait Anxiety Inventory and Infant Hip Worries Inventory, but higher or equal for EUROPEP.

#### Missing data

For the primary endpoint and principal secondary endpoint the data collection methods should identify qualifying episodes. Because of the nature of these data the conventional concept of missingness does not directly apply (eg, we will not have individually randomised subjects who cannot be followed up). However, if a practice withdraws from the trial, we will explore the consequences of this action by assuming a poor outcome among that practice if in the intervention group and a good outcome if in the control condition, to identify the potential consequences of their withdrawal. Complete case analyses will be conducted for secondary outcomes. If there is a mismatch between practices in the two treatment conditions, we will consider undertaking joint models examining simultaneously the binomial of missingness and the outcome measure of interest.

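### Complete-case analysis of the repeated clinician questionnaire ignores earlier scores already collected, so its arm difference can be biased even when dropout rates match

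*Protocol article*

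**What the plan says.** The Missing data section treats the primary and principal secondary endpoints separately, because they are ascertained from records ("For the primary endpoint and principal secondary endpoint the data collection methods should identify qualifying episodes"), and adds an extreme-case analysis for practices that withdraw. For everything else the commitment is "Complete case analyses will be conducted for secondary outcomes".

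The only departure allowed is discretionary: "If there is a mismatch between practices in the two treatment conditions, we will consider undertaking joint models", the models being ones "examining simultaneously the binomial of missingness and the outcome measure of interest". Mismatch is not defined; the natural reading is that missingness differs between the arms.

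Under Quantitative outcome measures the planned comparison is "We will summarise scores by instrument, accounting for practices and report difference in group means for each treatment arm". Neither baseline nor earlier scores are mentioned.

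Table 1 lists the "Theoretical Domains Framework questionnaire" at five times: baseline, within 2 weeks of the intervention, 3 months, 15 months and 2 years.

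**The concern.** A complete-case difference in means at a follow-up time uses only those who responded. If GPs who stop responding had different earlier scores from those who continue, the remaining sample is selected. When the selection works differently in the two arms, the arm difference is distorted. The earlier scores that could correct this are in the database but play no part in the stated analysis.

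The trigger for doing more is also a weak safeguard. Comparing how much is missing in each arm says nothing about why it is missing. Different reasons are plausible here: Strategies to mitigate potential bias accepts that GPs cannot be blinded, and only one arm receives a checklist and video to like or dislike. GPs unimpressed by the aid might stop returning forms in that arm while overstretched GPs stop in the control arm, with similar rates in both.

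The process evaluation is meant to explain the trial result. If disaffected GPs leave the aid arm's data, attitudes there will look more favourable than they are.

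**Working it through.** **Plan's own figures.** The article gives no response rate, dropout rate or correlation for any questionnaire, so there is nothing to reproduce on this point. The trial size of 76 practices per group concerns the primary endpoint and does not depend on it.

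**Which instruments are affected.**
- Theoretical Domains Framework: five times including baseline (Table 1). Affected.
- Fidelity questionnaire: four times (Table 1), but Clinician level says that the questionnaire on use of the aid goes to intervention GPs only. There is no clear arm contrast to bias.
- EQ-5D: two times (Table 1), but its only described use is the cost–utility work with 20 carers (Long run cost–utility analysis).
- State-Trait Anxiety, Infant Hip Worries, EUROPEP and CHU-9D: one time each, no baseline. Complete case equals available case, and there are no earlier scores to use.

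**Size of the bias.** All inputs are assumptions.
- Baseline score b is standard normal; follow-up score y = ρb + √(1 − ρ²)e, with e standard normal. The true arm difference is 0.
- The probability of dropout is expit(c + s·b). The constant c is set so that each arm loses the same fraction d.
- Same mechanism: s = 1 in both arms. One arm: s = 1 in one, 0 in the other. Opposite: s = 1 and −1.
- ρ = 0.3, 0.5, 0.7; d = 10%, 20%, 30%; 400,000 simulated respondents per arm, so that simulation error is small.

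Because dropout depends only on b,

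bias = ρ × (mean b among responders in one arm − mean b among responders in the other).

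Complete-case difference in SD units (truth 0; sign depends on which arm is selected):

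| ρ | Dropout, each arm | Same mechanism | Selective in one arm | Opposite mechanisms |
|---|---|---|---|---|
| 0.3 | 10% | 0.002 | 0.029 | 0.053 |
| 0.3 | 20% | 0.002 | 0.049 | 0.102 |
| 0.3 | 30% | 0.000 | 0.079 | 0.151 |
| 0.5 | 10% | 0.001 | 0.049 | 0.093 |
| 0.5 | 20% | −0.001 | 0.088 | 0.176 |
| 0.5 | 30% | 0.001 | 0.127 | 0.254 |
| 0.7 | 10% | −0.001 | 0.066 | 0.128 |
| 0.7 | 20% | 0.004 | 0.125 | 0.244 |
| 0.7 | 30% | −0.001 | 0.179 | 0.355 |

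The formula explains the pattern. At ρ = 0.5 and 20% dropout, selection in one arm shifts that arm's mean baseline by 0.088/0.5 = 0.176 SD. With opposite selection the two shifts add to 0.352, and 0.5 × 0.352 = 0.176.

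Adjusting the same responders for their observed baseline brings the difference to within 0.004 SD of 0 in every row. That result is built in, because simulated dropout depends only on the observed baseline. It shows what the collected scores can remove, not that they would remove every bias.

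**The case against.** The best case for the plan has four parts.

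1. The outcomes named for arm comparison under Quantitative outcome measures (State-Trait Anxiety, Infant Hip Worries, EUROPEP) are each measured once, so the repeated-measures argument does not reach them. This stands, and it limits the point to one questionnaire.

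2. The Theoretical Domains Framework appears only in Table 1. The clinician attitude endpoint in the text is a measure based on the theory of planned behaviour, taken at 12 weeks and at trial completion, and no longitudinal contrast is described. Interviews and observations also feed the process evaluation. This lowers the importance. It does not remove the point, because clinician process data are to be collected at all 152 sites and the stated rule covers them.

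3. The fallback joint models could address informative missingness. True, but they are only to be considered, on a condition that is not defined.

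4. Model detail belongs in a SAP, which is not shown. That would answer a complaint about omission. Here the article commits to a method and to a trigger.

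A reader might also infer heavy loss of partial responders. With independent 80% response per wave, only 0.8^5 = 33% of GPs would be complete over five waves. That needs complete case to mean present at every wave, which the article does not say; a comparison at each time point using all who responded then is equally consistent with the text.

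**Conclusion.** The point holds for the repeated clinician questionnaire. A method that ignores available scores is fixed, and its safeguard may not respond when rates match but reasons differ. Under the assumed 10–30% dropout and correlation of 0.3–0.7, with dropout log-odds changing by 1 per SD of baseline, the bias is about 0.03–0.18 SD with selection in one arm and 0.05–0.36 SD with opposite selection. It is about zero if dropout works the same way in both arms, so it is a possibility to guard against, not a prediction.

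Two stronger readings are not supported. One is that secondary outcomes in general are compromised: most questionnaires are measured once or have no described arm contrast, and late diagnoses come from record linkage. The other is a bias near 0.3 SD as the expected size. A five-wave scenario with selective dropout in the aid arm only and nearly half of GPs missing by the last wave gives 0.28 SD, but it is one unfavourable scenario, and none of its inputs is in the article.

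The importance is minor. The primary and principal secondary conclusions do not change.

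**What to change.** For the Theoretical Domains Framework questionnaire, replace the complete-case rule with a linear mixed model on all available scores:
- fixed effects for arm, time, arm-by-time, baseline score and practice-size stratum;
- random effects for practice and respondent.

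Run two sensitivity analyses regardless of whether missingness rates differ between the arms: the complete-case analysis and one prespecified missing-not-at-random analysis. The mismatch condition is then not needed for this outcome.

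Leave State-Trait Anxiety, Infant Hip Worries, EUROPEP and CHU-9D as available-case comparisons that account for practice. Do not apply an arm contrast to the use-of-aid questionnaire sent to intervention GPs only.

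The cost is a change of wording and one extra standard model; no new data are needed. The downside is reliance on data being missing at random given the observed scores, which the missing-not-at-random analysis is there to probe.

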### Health economics

#### Cost analysis

We will analyse the cost associated with the intervention compared with usual practice for the entire trial period, and examine costs from the perspective of the NHS and of families. The cost components included in main analysis are: cost of 6 weeks in both intervention arms; any subsequent referrals, diagnostic tests and treatment. We will collect costs about GP time, which we will multiply by unit costs from routine sources.^25^

#### Within-trial cost-effectiveness analysis

With the costs described above we will produce a dataset of patient-level within-trial costs and outcomes. We will calculate the incremental cost per clinically insignificant referral avoided and the incremental cost per late diagnosis avoided. Using bootstrapping of the mean cost and outcomes differences, we will estimate confidence intervals around the incremental cost-effectiveness ratios.^26^ With the bootstrap replications, we will construct a cost-effectiveness acceptability curve to show the probability that the aid is cost-effective for different values of NHS willingness to pay for outcomes. We will perform deterministic sensitivity analyses.

#### Long run cost–utility analysis

We will use several measures to evaluate the lifetime cost-effectiveness of the intervention. We will ask 20 carers of infants aged 2–4 years to complete (1) on behalf of their children the Child-Health-utility-9D^20^ and (2) for themselves the EQ-5D-5L,^27^ both measure health-related quality of life.

#### Cost–benefit analysis

With data from the trial about the impact of the intervention on appropriate referrals, we will calculate the monetary value that parents place on the intervention using willingness-to-pay methodology.^28^ This will provide an estimate of the monetary value of the additional benefits (positive/negative) of the intervention. We will calculate the net benefit of the intervention by subtracting the incremental cost of the aid, as calculated above from the trial data, from the monetary value of the additional benefit. Following recruitment of the last infant in the trial, we will recruit 200 carers of infants undergoing the 6-week check from trial-participating practices. These will be 100 carers whose infants will be referred to secondary care as a consequence of the 6-week check and 100 who will not. They will complete a self-report questionnaire that utilised several techniques^28^ to elicit willingness-to-pay values. We will calculate willingness-to-pay values for the whole sample and test for variations based on socio-demographic groups and referral to secondary care.

